#### Assessor-rated outcomes

Assessor-rated outcomes are summarized in Table 3. These consist of gold-standard general motor tests (Movement Disorders Society Universal Parkinson’s Disease Rating Scale part III, or MDS-UPDRS part III) and non-motor tests (symptoms from the MDS Non-motor symptoms scale, or NMSS), supplemented with specific tests for bradykinesia (Purdue pegboard test [52]), gait (Timed Up & Go Test [53]), balance (Mini-BESTest [54]) and quantified versions of the UPDRS items on tremor and pronation-supination (performed using accelerometry). These secondary outcomes are measured 30 min post-intervention, after which hypoxic preconditioning is believed to have its initial first window effects peak. After 30 min, the acute effects of hypoxia therapy peak, as shown in people with a cervical spinal cord injury [55], with the second window only occurring approximately 3 h post-intervention.

Various selected outcomes, including the UPDRS part III, are sensitive to the Hawthorne effect: individuals with PD try to perform as good as possible due to the awareness of being observed. To mitigate such effects, the placebo condition is added, for which the multiple N-of-1 design is also particularly suited [31, 36, 56].

Baseline characteristics that will be collected include age, gender, H&Y, quality of life (Parkinson’s disease questionnaire 39 [57]) and other medication. Potential effect modifiers include levodopa-equivalent dose (LED), sleep quality (4-point ordinal scale) and physical activity (International Physical Activity Questionnaire – Short Form, IPAQ-SF [58]) and these will be measured during every pre-intervention phase.

#### Mechanistic markers

Lastly, three markers will be measured in serum, which serve as a hypothesis-generating addition to our study. These measures may provide insight into potential pathways involved in the (individual) responses to hypoxia in our study. These measures include platelet-derived growth factor receptor β (PDGFRβ), cortisol and erythropoietin (EPO).

PDGFRβ is a pericyte-shedded marker in response to hypoxia [59–62] and is associated with blood–brain barrier (BBB) permeability [60, 61, 63–65]. Disruption of the BBB is a central process involved in PD pathophysiology [66] and therefore, acute effects of hypoxia therapy on PDGFRβ would give insight in the influence that hypoxia might have on BBB integrity in the long term [65].

Cortisol is a marker of physiological and mental stress and is hypothesized to rise during systemic hypoxic challenges [67]. As stress is one of the main determinants of variations in symptom severity, we investigate whether cortisol release might be associated with the short-term symptomatic efficacy of hypoxia-based interventions. This will give insight in whether hypoxia has beneficial influence on the stress system, or that the physiological stress results in fatigue and mental stress, thus worsening PD symptoms in the short-term. Cortisol is measured twice pre-intervention and three times post-intervention, because of its concentration changing with circadian rhythm.

EPO is a protein that is primarily shedded peripherally by the kidney. Although it is employed as a marker of hypoxic dose, attention for its role in neuroprotection has risen in recent years [68]. In preclinical PD models, it prevents neurotoxicity and preserves neuronal functioning [69, 70].

All outcome measures are summarized in further detail in Supplementary Fig. 1.

### Statistical analysis

All data will be collected using direct entry in CastorEDC, a widely used electronic data capture system for clinical data.

#### Analysis of primary study parameters

Safety outcomes will be analyzed using descriptive statistics of total number and percentages of adverse events, number of serious reversible or irreversible adverse events and vital parameters. Feasibility outcomes will be analyzed using descriptive statistics of feasibility outcomes including the feasibility questionnaire sum score and domain-specific scores.

### Secondary study parameters

#### Bayesian analysis

We will use a Bayesian model for the analysis of individual and aggregated N-of-1 trial results. This model allows for a direct estimation of the posterior probability that a treatment results in a clinically beneficial effect [32, 71–73]. The treatment effects resulting from the four different hypoxia protocols will be estimated per level of interest (i.e. the individual and group level). Every secondary outcome scored using the 10-point Likert scale will be modeled assuming a normal distribution centered around the patient’s true mean and variance for each protocol. If the posterior probability of reaching a 0.75-point difference between the secondary outcome after treatment and at baseline is greater than 80%, treatments are considered effective. Treatments are considered ineffective if the same posterior probability is less than 20%. Every treatment day has its own baseline (pre-intervention tests are performed) in order to further reduce period effects. The minimal clinically important difference for the secondary outcome MDS-UPDRS part III and Mini-BESTest is 4. One additional analysis will be performed including baseline characteristics and effect modifiers (see *Assessor-rated outcomes)* as covariates. Bayesian analyses will be performed using *JAGS* version 3.4.1 [74], run from *R* [75] using the package *rjags* [76].

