**Methods/Design:**

In 20 individuals with PD, we will investigate the safety, tolerability and short-term symptomatic efficacy of continuous and intermittent hypoxia using individual, double-blind, randomized placebo-controlled N-of-1 trials. This design allows for dose finding and for including more individualized outcomes, as each individual serves as its own control. A wide range of exploratory outcomes is deployed, including the Movement Disorders Society Unified Parkinson’s Disease Rating scale (MDS-UPDRS) part III, Timed Up & Go Test, Mini Balance Evaluation Systems (MiniBES) test and wrist accelerometry. Also, self-reported impression of overall symptoms, motor and non-motor symptoms and urge to take dopaminergic medication will be assessed on a 10-point Likert scale. As part of a hypothesis-generating part of the study, we also deploy several exploratory outcomes to probe possible underlying mechanisms of action, including cortisol, erythropoietin and platelet-derived growth factor β. Efficacy will be assessed primarily by a Bayesian analysis.

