### Study population

Twenty individuals with a diagnosis of PD (established by a neurologist according to the international Movement Disorder Society criteria) and Hoehn & Yahr stages between 1.5 and 3 will be included. Higher Hoehn & Yahr stages will be excluded for two reasons: firstly because of the significantly greater damage to dopaminergic pathways in advanced PD, which might limit the identification of nigrostriatal-mediated effects of hypoxia-based interventions; and secondly because of the high burden of testing participants in the OFF state in this more severely affected population. We aim to enrich our study population with individuals that have experienced (subjective) positive symptomatic effects at high altitude. In addition, we aim to include at least five individuals without prior experience with the positive effects of high altitude on their symptoms. This enrichment approach ensures that participants are more likely to be responders and allows us to validate our approach to identify each individual’s optimal protocol for clinical benefit. We believe that the selection bias introduced by our approach is justifiable because of the study’s explorative nature. In addition, PD is a very heterogeneous disease, for which a one-size-fits-all treatment approach is unlikely to be successful. Therefore, we wish to investigate for which individuals this therapy could be beneficial and the proposed approach is likely to be most promising. Main exclusion criteria relate to cardiorespiratory comorbidity and unstable PD medication. All inclusion and exclusion criteria can be found in Table 1.

**Table 1 Tab1:** Inclusion and exclusion criteria

Inclusion criteria	Exclusion criteria
Clinical diagnosis of Parkinson’s disease by a movement-disorder specialized neurologist	Individuals with diseases leading to restrictive and obstructive pulmonary diseases, pulmonary diffusion deficits, apnea and cardiac output deficits, such as pulmonary fibrosis, COPD, sleep apnea or excessive alcoholic intake, and congestive heart failure respectively
Hoehn and Yahr staging 1.5 to 3	Arterial blood gas abnormalities at screening day
Age > 18 years	Individuals with shortness of breath or other airway or breathing-related inconvenience related to lack of dopaminergic medication will be excluded

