### Intervention

We will study the response to multiple exposures of different pre-selected hypoxia protocols per participant, as at present there is no conclusive evidence for the effect of different hypoxia stimuli. This will optimize the chances for any changes in outcomes being identified, and allowing the possibility of defining the optimal dose of hypoxia as a therapeutic intervention individually. The selection of interventions was based on multiple studies that investigated and reviewed the hypoxia regimes that are currently perceived as being most effective [38–43]. In this N-of-1 trial design, every participant will receive two sets of five different conditions, with one being the placebo and the other four variants of an active intervention, consisting of either intermittent or continuous hypoxia at FiO2 0.127 (~ 4000 m) and 0.163 (~ 2000 m). All interventions are administered twice to enhance intra-individual discriminative power towards a sufficiently low or high probability (see *Statistical Analysis*). As it is shown that hypoxic preconditioning effects may linger for up to four days [44], a wash-out of at least five days between sessions will be built-in. Once a week, one of the following five conditions will be administered following the order resulting from a Latin square randomization (see *Statistical Analysis*):

Active interventions:Continuous hypoxia for 45 min, at ~ 2000 m (16.3% O_2_)Continuous hypoxia for 45 min, at ~ 4000 m (12.7% O_2_)Intermittent hypoxia with 5 × 5-min at ~ 2000 m (16.3% O_2_), interspersed with 5-min normoxic recoveryIntermittent hypoxia with 5 × 5-min at ~ 4000 m (12.7% O_2_), interspersed with 5-min normoxic recoveryPlacebo intervention:Continuous normoxia for 45 min (20.9% O_2_)

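### The design is presented as allowing dose finding and an individual optimal protocol, but the only stated decision rule judges each hypoxia protocol alone and no between-protocol contrast is given

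*Protocol article*

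**What the plan says.** Three places in the Protocol article give a comparative purpose.

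- Abstract, Methods/Design: "This design allows for dose finding".
- Study population, in support of enriching for people who improved at altitude: the approach "allows us to validate our approach to identify each individual’s optimal protocol for clinical benefit".
- Intervention (the description of the conditions), in support of several protocols per person: "allowing the possibility of defining the optimal dose of hypoxia as a therapeutic intervention individually".

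All three are design rationale. Dose finding is not among the numbered primary or secondary objectives.

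On the design, "every participant will receive two sets of five different conditions, with one being the placebo and the other four variants of an active intervention". The four active conditions cross two oxygen levels (16.3% and 12.7%) with two patterns (continuous and intermittent). On replication, "All interventions are administered twice to enhance intra-individual discriminative power towards a sufficiently low or high probability".

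The Bayesian analysis section says: "The treatment effects resulting from the four different hypoxia protocols will be estimated per level of interest", meaning the individual and the group. The decision rule follows there: "If the posterior probability of reaching a 0.75-point difference between the secondary outcome after treatment and at baseline is greater than 80" per cent, the treatment is called effective; below 20% it is called ineffective. Between the two there is no verdict. The Frequentist analysis section adds dependent t tests at group level and does not say which conditions are compared.

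**The concern.** Optimal is a comparative word. To say that one protocol is a person's best, the protocols have to be compared with each other. The stated rule compares each protocol only with its own baseline and a threshold. The two sessions per protocol are justified by their ability to push that same single-protocol probability towards a high or low value, so the replication is also tied to a rule that does not answer the dose question.

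If nothing else is specified, the only materials for naming an optimum are differing labels or the largest point estimate. One protocol passing a threshold while another does not is weak evidence that the two differ, and with two sessions each it will happen often when they do not differ at all. A missing placebo contrast is a separate matter: labels formed against placebo and then compared would have the same weakness.

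**Working it through.** The article states no SD, power or error rate for the rule, so there is no figure of its own to reproduce. The check asks how often four protocols with the same true effect receive different labels in one participant.

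**Inputs from the article.** Four active protocols; two sessions each; threshold 0.75 points; cut-offs 80% and 20%.

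**Assumptions.** Flat prior; known session-to-session SD of the change score, 0.5 to 2.0 points; common true change d of 0 to 2.0 points.

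**Formula.** The mean of two sessions has SE = SD/√2. The label is effective if (mean − 0.75)/SE > 0.8416, ineffective if it is < −0.8416, and otherwise inconclusive. With label probabilities pE, pN and pI (effective, inconclusive, ineffective):

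- labels not all the same: 1 − (pE⁴ + pN⁴ + pI⁴)
- effective and ineffective both present: 1 − (1 − pE)⁴ − (1 − pI)⁴ + pN⁴

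**True change exactly 0.75.** pE = 0.20, pN = 0.60, pI = 0.20, whatever the SD. Labels not all the same: 1 − (0.0016 + 0.1296 + 0.0016) = 0.867. Both extremes present: 1 − 2 × 0.4096 + 0.1296 = 0.310.

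**SD 1.0, true change 1.5.** SE = 0.707; pE = 0.587, pN = 0.385, pI = 0.029; labels not all the same in 86%.

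Each cell gives labels not all the same / effective beside ineffective:

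| Session SD | d = 0 or 1.5 | d = 0.75 | d = 2.0 |
|---|---|---|---|
| 0.5 | 35% / 1% | 87% / 31% | 1% / <1% |
| 0.75 | 73% / 5% | 87% / 31% | 24% / <1% |
| 1.0 | 86% / 10% | 87% / 31% | 54% / 2% |
| 1.5 | 90% / 19% | 87% / 31% | 83% / 8% |
| 2.0 | 90% / 23% | 87% / 31% | 89% / 14% |

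**Other models (simulation, 100,000 participants per cell, true change 0 to 1.5).**

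- Separate unknown variance per protocol (t, 1 df), SD 0.75 to 2.0: 84 to 90%.
- Variance pooled within participant (t, 5 df), SD 1 to 2: 82 to 86%.
- Effect taken against placebo, SD 1 to 2: 70 to 75%.
- Shrinkage to a known group mean (between-protocol SD 0.25 to 1, session SD 0.5 to 1.5): from about 0% to 90%.

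**Largest estimate as the optimum.** With equal true effects, the mean gap between the highest and lowest of four estimates is about 2.06 × SE: 1.1 points at SD 0.75 and 2.9 points at SD 2.0, against a threshold of 0.75.

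**Group level (N = 20, person effect shared across protocols).** I took person SD 0.5 with session SD 1.0, and 1.0 with 2.0. Labels differ in about 81% at a true change of 0.75, but in only 0.4 to 37% at 0 or 1.5.

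**What a direct comparison would give, per participant.**

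- One pair of protocols: SE = SD × √(1/2 + 1/2) = 1.0 × SD.
- A main effect over the 2×2 layout, four sessions against four: SE = SD × √(1/4 + 1/4) = 0.71 × SD.
- True difference 1.0, SD 1.0: the chance that the posterior probability of a difference exceeds 90% is 1 − Φ(1.28 − 1/SE). This is 39% for a pair and 55% for a main effect. With no true difference it is 10% for both.
- Four equal protocols: some protocol has a probability of being best above 80% in about 11 to 12% of participants, and above 90% in about 3 to 3.5%.

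**The case against.** The strongest reply is that this is a condensed article. A between-protocol contrast may stand in the full protocol or analysis plan, and nothing printed rules it out. The model estimates all four effects per person, so contrasts can be derived from it. This stands in part: the point is a mismatch between stated purpose and stated rule, and does not show that no contrast is planned anywhere. But the article chose to fix the rule, its thresholds and the reason for two replicates, and it can be asked to make these fit the purpose it gives.

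Four stronger readings are tempting and not supported.

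- **That labels will be used to rank protocols or to assign a participant a best one.** No section says so. The nearest downstream use, in Sample size, takes effect sizes and SDs of protocols found clinically meaningful at group level into a future calculation. That is screening against a threshold, not ranking.
- **That dose finding is a committed objective.** It appears only as rationale, and the Intervention section words it as a possibility.
- **That a disagreement rate near 75 to 90% is a property of this trial.** The rate depends on SD, effect size and prior, none of which is given, and it counts inconclusive as a label. An effective label beside an inconclusive one asserts no difference.
- **That group-level conclusions would mostly be noise.** Group-level disagreement is high only when the true change lies near 0.75.

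It is also fair to say that the precision gain from the 2×2 analysis helps only if the interaction between oxygen level and pattern is small.

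**Conclusion.** The concern holds as a mismatch between purpose and rule. As written, the analysis cannot support a statement about a person's optimal dose or protocol, because the rule contains no comparison between protocols and none is named elsewhere in the article. This part rests on the text alone.

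The size rests on assumptions. At individual level, with a flat prior, known session SD of 0.75 to 2.0 and a common true change of 0 to 1.5, equal protocols get labels that are not all the same in about 73 to 90% of participants, and directly opposed labels in about 5 to 31%. The first figure drops to 1% at SD 0.5 with a true change of 2.0, and could be far lower than 73% under hierarchical shrinkage, which a model for individual and aggregated results may use. The sponsor should make the change, since the remedy is nearly free. It does not put the safety or feasibility outcomes in question.

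**What to change.** In the Bayesian analysis section, state that any dose or optimal-protocol conclusion will rest only on between-protocol contrasts from the same model:

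1. The oxygen-level main effect (12.7% against 16.3%), the pattern main effect (continuous against intermittent) and their interaction, per individual and for the group, with the interaction always shown beside the main effects.
2. The posterior probability that each protocol is the best of the four. Name an optimum only above a cut-off that the sponsor sets in advance, and otherwise report no distinguishable optimum. The error rates under Working can inform that choice.
3. A sentence saying that differing effective and ineffective labels are not evidence that protocols differ.
4. A note that the pattern contrast also carries different hypoxic time: 45 minutes continuous against 5 × 5 = 25 minutes intermittent.

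The cost is wording and a few derived quantities from the planned model, with no new data. The downside is that fewer participants will be reported as having an identified optimum, and the main effects are hard to interpret if the interaction is large.

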### Sample size

Because this is the first study in which the clinical effects of hypoxia therapy will be measured in PD and because of the study’s exploratory nature, a formal sample size calculation cannot be performed. A previously published power and sample size simulation study aggregated N-of-1 trials with multiple cycles of intervention and placebo per participant, and found that under certain assumptions N-of-1 trials needed only one-third of the sample size of an RCT to reach a similar power and type I error [36]. This was confirmed in a recent aggregated N-of-1 trial that investigated the effectiveness of the drug mexiletine in myotonia, in which the aggregated N-of-1 trial showed comparable treatments effects on a personalized Likert scale (i.e., the same outcome measure as we propose) with inclusion of 11 participants vs 57 participants in a traditional cross-over RCT [32]. Our proposed sample size of 20 was motivated by this work, in combination with the sample size consensus for feasibility studies of 20–30 [37].

The observed effect sizes and standard deviations of the different hypoxia protocols that are found to be clinically meaningful at the participant group level in this study (*N* = 20) will be used to simulate a power and sample size calculation for a future follow-up study that will be powered for efficacy using the data generated in this study.

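### The Bayesian model as worded gives each patient a separate variance for each protocol, estimated from two sessions (one degree of freedom), so individual verdicts lean heavily on the variance prior

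*Protocol article*

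**What the plan says.** Three statements in the protocol article bear on this point.

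- **Model** (Bayesian analysis): every outcome on the 10-point Likert scale is taken as normal, around the patient's "true mean and variance for each protocol".
- **Verdict** (same section): effects are to be "estimated per level of interest (i.e. the individual and group level"). The upper limit is put on a posterior probability: when that of a "0.75-point difference between the secondary outcome after treatment and at baseline is greater than 80%, treatments are considered effective". For the lower limit, "Treatments are considered ineffective if the same posterior probability is less than 20" per cent. Between the two limits there is no verdict. The section adds that each treatment day has its own pre-intervention baseline.
- **Replication** (Intervention): "every participant will receive two sets of five different conditions", one of them placebo. The reason given is: "All interventions are administered twice to enhance intra-individual discriminative power towards a sufficiently low or high probability".

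The article states no prior, no expected standard deviation and no sharing of variance across protocols or patients. The Sample size section says that no formal calculation could be done.

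**The concern.** A variance specific to one patient and one protocol can be learned only from the sessions in which that patient received that protocol, and there are two. They leave one degree of freedom. Table 3 lists ten post-intervention ratings per session (seven on the day, three on the following mornings). They share the conditions of that session, so they show how symptoms vary within a session and not how sessions differ. The seven-day home baseline adds readings but no further sessions of any protocol.

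With one degree of freedom the posterior for the mean is very heavy-tailed, or its width is set largely by the prior on the variance. That works against the stated reason for giving each condition twice, which is to move individual probabilities towards one limit or the other. Individual verdicts are a stated purpose of the N-of-1 design, so the variance structure matters even though these outcomes are secondary.

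**Working it through.** The article gives no verdict probability or power, so there is no figure to reproduce. I evaluated the written rule directly.

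**Inputs from the article.** 5 conditions × 2 sessions = 10 sessions per patient; 20 patients; threshold 0.75 points; limits 80% and 20%; change measured from same-day baseline.

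**Assumptions.** One change score per session; session-to-session SD of that score 0.5 to 2.0 points; flat prior on the mean and reference prior on the variance, unless stated otherwise.

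**Degrees of freedom.**
- Separate variance per patient and protocol: 2 − 1 = 1.
- Shared across conditions within a patient: 5 × (2 − 1) = 5.
- Shared across all patients as well: 20 × 5 × 1 = 100.

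**Rule.** Let t = (mean change − 0.75) / (s/√2). The posterior of the mean is a t distribution, so the verdict is effective if t > c and ineffective if t < −c, where c is the 80th percentile of t: 1.376 (1 df), 0.920 (5 df), 0.845 (100 df). The verdict probabilities follow from the noncentral t with noncentrality (true change − 0.75) × √2 / SD. For example, a true change of 2.0 at SD 1.0 gives 1.25 × 1.414 / 1.0 = 1.768.

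**Probability of an effective verdict**

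| SD | True change | 1 df | 5 df | 100 df |
|---|---|---|---|---|
| 1.0 | 0 (false) | 4.0% | 3.1% | 2.9% |
| 1.0 | 1.5 | 51% | 57% | 59% |
| 1.0 | 2.0 | 71% | 80% | 82% |
| 1.0 | 2.5 | 86% | 94% | 95% |
| 1.5 | 0 (false) | 7.4% | 6.4% | 6.1% |
| 1.5 | 2.5 | 68% | 77% | 79% |

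Most of the gain is already reached at 5 df, so equal variances across patients need not be assumed.

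**Share with no verdict, true change 0 or 1.5**

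| SD | 1 df | 5 df | 100 df |
|---|---|---|---|
| 0.5 | 21% | 11% | 10% |
| 0.75 | 37% | 29% | 27% |
| 1.0 | 45% | 40% | 39% |
| 1.5 | 53% | 50% | 49% |
| 2.0 | 56% | 54% | 54% |

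The share passes 50% at SD 1.24 with 1 df and at SD 1.50 with 5 df. At a true change of exactly 0.75, each verdict has probability 20% and 60% are undecided, whatever the df.

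**Dependence on the prior (separate variance).** At SD 1.0 and a true change of 0 or 1.5, inverse-gamma priors with both parameters at 0.001, 0.5, 1 or 2 leave 42% to 46% undecided, close to the reference prior. A Uniform(0,10) prior on the SD leaves over 70% undecided. Over SD 0.5 to 1.5 and true changes of 0, 0.75 and 1.5, its undecided share runs from about 70% to 95%. Two priors that both look vague can therefore give quite different sets of verdicts.

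**Half-point scale.** If change scores fall on half points, the two replicates coincide in about 27% (SD 0.5), 14% (SD 1.0) or 9% (SD 1.5) of cases. The sample variance is then zero and the prior alone sets the spread.

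**The case against.** The strongest reply is that one clause in a condensed article is being read too literally. It is loosely worded, since a distribution is not centred on a variance. The section also promises a model for individual and aggregated results, and it does not exclude hierarchical priors on the variances. Priors and the handling of repeated ratings are commonly left to a fuller document. This stands in part: the absence of priors or code is no fault in the article. But the clause does state a variance structure, and that structure fits badly with two administrations per protocol.

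A second reply is that the effect is small and the outcomes are secondary in an exploratory study. That also stands, and it limits the weight of the point.

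A reader might go further and infer that individual verdicts will mostly be inconclusive, that the rule is miscalibrated at its own threshold, or that pooling would buy power with more false effective verdicts. The article does not support any of these.

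- *Mostly inconclusive* needs an SD above about 1.2, a true change near 0.75 or a very vague prior on the SD. The article fixes none of them.
- *Miscalibration* and a larger power loss appear if the rule is applied to an active-minus-placebo contrast. At SD 1.0 and a benefit of 1.5, that contrast gives about 27% with separate variances against 46% with pooled ones, and at 0.75 it fires about 11% against 20%. The written rule uses change from baseline; under the reference prior it fires at 20% for any df when the true change is 0.75.
- *More false effective verdicts* also belongs to that contrast. Under the written rule they fall.

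**Conclusion.** The point holds in a limited form. As worded, an individual verdict rests on a variance with one degree of freedom and depends heavily on the variance prior. Under the written rule with a reference prior, sharing the variance within a patient adds 6 to 9 percentage points to the probability of a correct effective verdict at SD 1.0 and true changes of 1.5 to 2.5. It lowers false effective verdicts by about 1 point.

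Much of the indecision comes from having only two sessions, and no variance model removes that: at SD 1.0 and a true change of 1.5, sharing moves the undecided share only from 45% to 40%. The sizes rest on assumed SDs and priors and on one change score per session. If the full protocol or analysis plan already shares the variance, only the sentence in the article needs correcting.

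**What to change.** Replace the clause with one hierarchical model that has:

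- patient-by-protocol means;
- one session-level variance per patient, shared across the five conditions and partially pooled across patients;
- a session random effect, if several ratings per session enter the analysis.

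Give the variance priors alongside the model, with the simulated probability of each verdict over a range of SDs, so that a reader can see how far the prior drives the verdicts.

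The cost is a few lines of JAGS code and no change to the conduct of the trial. The downside is the assumption that session-to-session noise is similar across protocols. A sensitivity analysis with protocol-specific variances, partially pooled, can relax it.
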